**Protocol Summary**
Elderly patients with a hip fracture are a particularly vulnerable group with high morbidity and mortality (1-3) and some patients do not regain previous level of physical function (4, 5). The most recent Cochrane review that assesses the effect of physical therapy concludes evidence from randomized trials insufficient to determine the effectiveness of different types of exercise used in the rehabilitation after hip-fracture surgery (6).

Patients with a hip fracture admitted to Hvidovre Hospital have since September 2002 been treated in the fast track concept (7, 8) in a specialized unit at the Department of Orthopedic Surgery. The treatment is optimized and intensified regarding surgery, nutrition, pain management, physical therapy, etc. during hospitalization. Despite the optimized efforts, patients who are discharged directly to their own home after following a standard course are admitted in average 16 (SD 14) days and still some patients are discharged to 24hour rehabilitation units in the primary sector. A study from the unit has shown that 32 % of patients fall again within 6 months after discharge (9). Other data collected in the unit have shown that quadriceps muscle strength of the operated limb among patients discharged directly to their own home is less than 50% of the strength of the healthy limb (10), despite the fact that they have followed an optimized treatment course.

Despite no clear evidence, that strength training is long term effective for patients with a hip fracture (6), it is still considered an essential component of the rehabilitation process. It is well known that resistance training increases muscle strength in healthy elderly people (11) and patients with a hip fracture, even when initiated 16 days after surgery at the earliest (12). This is also supported by two other studies where strength training was started at an even later time-point after discharge (13, 14). All three studies showed effects of strength training at the end of the intervention compared with the control group, but either there were too few participants or too short follow-up time to conclude on the effects of strength training as an intervention, as well as the intervention was implemented so late that the loss of muscle function already was established. Subsequently, since the elderly experience an average decrease in muscle strength of 15% after 10 days of bed rest (15, 16) and already has low muscle strength due to old age, early strength training in patients with hip fractures seems rational to avoid a major loss of strength and physical function. For example, a study among elective patients operated with total hip arthroplasty showed effect of strength training started immediately after surgery (17). It is unknown whether elderly patients with a hip fracture can participate in physical therapy including strength training started immediately after surgery and whether the effect is greater than physical therapy without strength training.
We therefore wish to perform *(1)* a study of the feasibility of strength training started the day after surgery, and *(2)* a randomized study with implementation of strength training the day after surgery, where 100 elderly patients with hip fractures admitted in the Hip fracture unit at Hvidovre Hospital are randomized to physical therapy with or without progressive resistance training.
The study is part of the "Hip fracture project", Department of Orthopedic Surgery, Hvidovre Hospital, and with an expected duration of 30 months. It should be emphasized that the investigation is not supported by or associated with the pharmaceutical industry, and none of the participants have financial or other interest in the study.
 

**Purpose of the study**Primary purpose:

Patients are characterized by a high average age, which for many patients are associated with sarcopenia (age-related loss of muscle mass, strength and physical function) (21) and a deterioration of this is a known result of a hip fracture. Data collected in the unit have shown that, despite this intensive rehabilitation program, the muscle strength in the operated limb among patients being discharged directly to the own home, represents less than 50% of the strength in the healthy limb (10), similar to levels seen in a previous study (22). In addition, the strength loss was significantly greater among patients with a trochanteric hip fracture, compared to patients with a cervical hip fracture and the degree of strength loss was strongly associated with the degree of swelling (edema) in the operated limb (10). The importance of fracture type is further demonstrated in a study showing that the probability of achieving independence in basic mobility assessed by the CAS and to return to the original housing is less for patients with a trochanteric fracture compared to patients with a cervical fracture (23). Strength training increases muscle strength in healthy elderly persons (11) and three studies have shown short-term effects of resistance training in patients with a hip fracture initiated at a later stage of the rehabilitation program (12-14) as well as in elective patients operated with total hip arthroplasty and starting strength training immediately after surgery (17). It is therefore considered rational to evaluate physical therapy including strength training, starting in the very early postoperative period in patients with a hip fracture.

**Study Design**
**Study type**
Part one: The study of the feasibility of strength training during hospitalization is planned conducted with 40 patients meeting the inclusion criteria for the randomized study. This project will be completed prior to the initiation of the randomized trial.

The randomized part of the study is conducted as a single-blind study:
 Randomization

Strength

Run in

Treatment period Follow up

Control

Test

Screening

Test

Time ____________________________________________________________________________________

Opr. 1st post opr. day 10th post opr. day/discharge 16 weeks

**Randomization**
Patients are randomized to one of two treatment groups. A computer compiles randomization list. Based on randomization, ​​envelopes are made with patient number, including allocation of patients to standard physiotherapy + strength training vs. standard physiotherapy without strength training as it is today with exercises and functional training. The envelopes are opened after inclusion for the individual patient only. The randomization list is kept in a sealed envelope by the clinically responsible. Patients are stratified by type of fracture, so that each group includes an equal number of cervical versus inter-/subtrochanteric fracture.

**Blinding**Randomized study: Patients, doctors, nurses and involved physical therapists are for obvious reasons not blinded, but test at inclusion, discharge, and 16 weeks will be carried out by blinded personnel without knowledge of treatment group.

**Timetable**Part one: The 40 patients are planned for inclusion in the period mid 2012 to ultimo 2012. This part of the study found strength training feasible and without pain or other adverse events associated.
Randomized part: Recruiting of the patients is expected to begin mid 2013 and the study is expected to extend over a period of approximately 18 months, provided the expected inclusion of 6 patients per month.

**Interruption**
The individual patient may withdraw from the study at any time. Patients may also be excluded from the study at any time based on the investigator's evaluation.

**Data registration**
All data relevant for the study are recorded in a specific ​​form. Data of each enrolled patient are listed in a personal form.

**Population**
Randomized part: Calculations have shown that in order to show a 30% reduction in the difference in strength between the operated and the healthy limb, with a significance level of 0.05 and 80% strength, 38 patients needs to be included in each group. Due to the expected dropout rate, 100 elderly patients admitted from their own homes to the acute ward with a hip fracture will be included.

**Inclusion criteria:**Patients aged ≥ 60 years admitted to the acute ward with a diagnosed hip fracture (cervical, pertrochanteric or subtrochanteric fracture) and
· Able to speak and understand the Danish language
· Able to give informed consent
· Home-dwelling with an independent physical function estimated as a New Mobility Score of ≥2 indoor.
**Exclusion Criteria:**
· Multiple fractures requiring surgery
· Postoperative surgical mobilization restriction
· Patient unwilling to participate in appropriate rehabilitation
· Terminal illness

· Patients who want an observer present at the information interview, but where such one is not available.

**Procedures
Part One:** Strength training is an optional treatment in the regular physical therapy treatment today, and will be attempted systematically implemented starting day 1 or 2 postoperatively. The aim is strength training conducted every weekday during in-hospital stay.

**Randomized part:**1. Information and provision of informed consent before or at the latest, on the 2nd postoperative day after admission.
2. Randomization to two groups of 50 patients performed by the project manager or one of the other investigators.

**Standard for physical therapy during hospitalization**

**Physical therapy including strength training**
Daily on weekdays (first 3 days after surgery including weekends) during hospitalization with a physical therapist focusing on independence in basic activities (same program as the control group, physical therapy without strength training) but also including:
Operated leg strength trained with knee-extension exercises 0-90 degrees. The starting position is sitting in the chair, on the bed or couch with 90-degree flexion of the knee. The concentric and eccentric movement is performed slowly and controlled and performed with ankle weights.
The strength training is conducted as follows from 1st postoperative day during hospitalization:
3 sets of 10 repetitions, 10 RM (repetition maximum) load.
Patients unable to complete the entire program on a given day, will perform as many sets and repetitions as possible.

**Physical therapy without strength training**
Exercising "ankle flexions" as bed exercises and hereafter daily exercise of: getting out of/in to the bed, chair raise/sit in chair, walking with suitable walking aid and climbing stairs during in-hospital stay.

**After discharge**
All patients follow standard rehabilitation course in the primary sector (usually up to 8 class exercises).

**Registrations**

# Primary outcomes

**Physiotherapy and Mobilization**
- **During in-hospital stay and at discharge:**
The New Mobility Score (NMS) (20, 24) is used for the assessment of pre-operative physical function. Patients are assessed at a daily basis on their ability to perform basic mobility tasks, defined as: getting out and into the bed, sit to stand from a chair and walking with relevant walking aid. The Cumulated Ambulation Score (18) is used to describe this level of basic mobility. Furthermore, the time recorded in the Timed Up and Go test (TUG) (25-27), and 10 meters walk (fast speed walking), which assesses functional mobility are registered upon discharge. The tests are part of the regular physical therapy conducted in the acute ward. In the event of a patient being unable to perform strength training or a given physical function independently, the limiting factors that apply are registered. The circumference of thigh and lower leg and – both fractured and healthy limb is measured at inclusion and discharge as in previous study (10).
Isometric strength is measured with a handheld dynamometer as early as possible after inclusion.
All re-tests are performed on the 10th postoperative day if possible and/or the day before discharge.

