**- 16. week post operatively follow up**

TUG, 10 Meter Walking test, NMS, isometric strength both limbs.

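### About seven outcomes are listed as primary, but the sample size covers only one between-limb strength difference, which has no time point and is not in that list

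*Protocol*

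**What the plan says.** - **Outcome list.** In the Registrations section, the heading "Primary outcomes" covers everything up to the heading for secondary outcomes. In hospital or at discharge this means daily CAS, TUG, 10 m fast walk, thigh and lower-leg circumference, and isometric strength. The 16-week subsection adds "TUG, 10 Meter Walking test, NMS, isometric strength both limbs".
- **Baseline item under the same heading.** "The New Mobility Score (NMS) (20, 24) is used for the assessment of pre-operative physical function".
- **Strength test in hospital.** "Isometric strength is measured with a handheld dynamometer as early as possible after inclusion", with re-tests on day 10 if possible and/or the day before discharge. The healthy limb is mentioned for circumference at these visits but not for strength. Both limbs are written for strength only at 16 weeks.
- **Sample size (Population).** The target is a "30% reduction in the difference in strength between the operated and the healthy limb". For this the section sets a level of 0.05 and a power of 80%, and arrives at 38 per group. Enrolment is 100 in all to allow for dropout. No time point, mean or standard deviation (SD) is given.
- **Analysis (Data processing and data analysis).** Repeated-measures ANOVA is the primary analysis. The text does not say to which outcome it applies or which result decides the trial.

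**The concern.** The primary list and the sample size do not describe the same thing. The list holds about seven outcomes, several of them measured twice. The sample size rests on one quantity, the strength gap between the limbs, which the list does not contain as an outcome. For the in-hospital visits the Protocol does not clearly say that both limbs are tested for strength, so it is not certain that the gap can be formed there.

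Two things are at stake. If the list is followed as written and each outcome is tested at 0.05, the chance of some positive primary result under no effect is well above 5%. If the error rate were instead shared across the list, the stated 80% power would no longer apply, even to strength.

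**Working it through.** **Inputs.** Level 0.05, power 80% and 38 per group come from the Population section. A two-sided test is assumed because sidedness is not stated. The outcome list comes from Registrations and its 16-week subsection. No correlation between outcomes is given, so a range from 0 to 0.7 is assumed.

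**1. The plan's own figure.** Without a mean gap or an SD, 38 per group can be neither reproduced nor refuted. It can be inverted to give the implied standardised effect:

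d = (z₀.₉₇₅ + z₀.₈₀) × √(2/n) = (1.960 + 0.842) × √(2/38) = 2.802 × 0.2294 = 0.643

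The noncentral t distribution gives 0.651. This is an implied value, not one that the Protocol states.

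**2. How many primary tests?**
- By outcome: CAS, TUG, 10 m walk, thigh circumference, lower-leg circumference, strength, NMS = 7. This fits a repeated-measures ANOVA that yields one group test per outcome across time.
- By outcome and time: 6 early (CAS, TUG, walk, two circumferences, strength) + 4 at week 16 (TUG, walk, NMS, strength) = 10.
- Pre-fracture NMS is a baseline variable and is not counted.

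**3. Chance of at least one false positive, each test at 0.05.** For independent tests this is 1 − 0.95ᵏ:
- k = 7: 1 − 0.95⁷ = 0.302
- k = 10: 1 − 0.95¹⁰ = 0.401

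With equally correlated normal test statistics:

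| Tests | r = 0 | r = 0.3 | r = 0.5 | r = 0.7 |
|---|---|---|---|---|
| 7 | 30% | 27% | 23% | 18% |
| 10 | 40% | 35% | 29% | 21% |

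**4. Power for strength if 0.05 were shared equally (Bonferroni).** The Protocol does not propose this; it only shows the price of keeping the whole list primary. At d = 0.651 and 38 per group, by noncentral t:
- k = 7, level 0.05/7 = 0.0071: power 53%
- k = 10, level 0.05/10 = 0.005: power 48%

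**5. With a single primary.** If one strength outcome at one time point is primary, k = 1, and 0.05, 80% and 38 per group apply as stated.

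**The case against.** The strongest reply is that the Protocol states 0.05 and 80% for the strength contrast alone and never claims them for a set of outcomes. That is correct, and nothing here shows those figures to be wrong for strength. A reader might infer that the sample size itself is in error; the documents do not support that.

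A second reply is that strength is the evident target. It is the only outcome used for sizing, the Lay Summary presents reduced strength loss as the direct effect from which fewer falls and better function follow, and the contents page has the heading in the singular. The list also mixes in plain record-keeping, such as the factors that limit exercise. This makes strength the likely intended primary outcome, so it would go too far to say that the Protocol gives no pointer to a deciding outcome. But the body text still labels the other measures as primary, and the time point stays open.

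Third, ten tests and 40% is a tempting headline. It needs both a split of early and week-16 results into separate tests and independence between them. The planned repeated-measures ANOVA may leave about seven tests, and repeated measures of the same function are unlikely to be independent. If the circumferences are explanatory, five tests remain, with 23% at independence (1 − 0.95⁵), 18% at correlation 0.5 and 15% at 0.7. The size therefore depends on the reading, but the rate exceeds 5% on all of them.

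Finally, a statistical analysis plan that is not shown may hold a multiplicity rule, so the lack of one here is not the point. The point is that the Protocol's own primary list and its sample size do not match.

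**Conclusion.** The concern holds in this form: the primary list and the powered quantity are not reconciled, and no time point is fixed for the powered quantity. The stated 0.05 and 80% belong to one between-limb strength contrast and do not extend to the listed primary set. Testing each listed outcome at 0.05 gives about 18–30% (seven tests) or 21–40% (ten tests) for at least one false-positive primary result. An equal split of the error rate would leave about 48–53% power for strength at 38 per group.

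The error rates rest on assumed equal correlations. The power figures rest on a two-sided test and on the effect implied by the Protocol's own n, level and power. Power for TUG, walking, CAS, NMS and circumference cannot be computed, because no effect or SD is given for them.

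A reader might also infer that the trial is powered on strength at day 10 or discharge. That visit suits an in-hospital intervention, but the Population section does not say so, and week 16 is the only visit at which strength in both limbs is written down.

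**What to change.** Align three sections of the Protocol (Population, Registrations, and Data processing and data analysis):

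1. Name the operated-versus-healthy limb difference in isometric strength as the sole primary outcome.
2. Have the sponsor state one time point for it, either day 10/discharge or week 16, and give the same time point in the sample-size paragraph and for the primary ANOVA contrast.
3. State that strength is measured in both limbs at inclusion and at that time point.
4. Make strength at the other time point, and TUG, 10 m walk, CAS, circumferences and week-16 NMS, secondary.
5. List pre-fracture NMS as a baseline variable.

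The multiplicity problem is then removed without more patients, because 38 per group was set for a single contrast. The cost is that a positive TUG, walking or mobility result can no longer be claimed as primary. The healthy limb must also be strength-tested in hospital if this is not already done. If the sponsor wants to keep several primary outcomes, the Protocol should state how the error rate is shared or ordered, and the trial should be sized for that rule.

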**Data processing and data analysis**

An assigned project number identifies all enrolled patients. At end of study, all personal identifiable data will be destroyed. Patients are informed orally and written, that data is stored and analyzed in a computer, the patient's anonymity will be ensured, and that the study complies with law of data protection. Assuming normally distributed data, the primary analysis will be repeated measures analysis of variance (ANOVA) to determine the systematic difference between the intervention and control group. Furthermore an intention-to-treat analysis will be carried out. The Data Inspectorate has approved the study J.no. 2007-41-1573.

**Financial disclosures**The study is part of the Hvidovre Hospital "Hip fracture project". It is emphasized that the study is not supported by the pharmaceutical industry or by any other institutions with financial interest in the studied problem, and that no participants in the project have financial or other interests in the studied problem.
Financial assistance for completion of the study will be applied for, but none of the potential sponsors in the project will have any influence or financial disclosure in the organization, implementation and interpretation of the data collected in the project.
 **Publication**The study results, both positive and negative, are planned for publication in an international English journal. The project manager prepares the manuscript, is corresponding author and is listed as the first author. All investigators are listed as authors.
Similarly, the results will be presented at national and international congresses. Provided positive experience with strength training for patients with a hip fracture, the procedure for this will be sought incorporated into national guidelines.

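### Limb circumference is filed under primary outcomes with no stated construct, derived variable or direction of benefit, so a between-arm change could not be read as benefit or harm

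*Protocol*

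**What the plan says.** In the Registrations section, the heading "Primary outcomes" covers a block on physiotherapy and mobilization. In that block the protocol writes: "The circumference of thigh and lower leg and – both fractured and healthy limb is measured at inclusion and discharge", adding that this follows an earlier study from the same unit (reference 10, whose listed title names thigh edema). The same block holds the New Mobility Score, the Cumulated Ambulation Score, Timed Up and Go, the 10-metre walk, factors limiting performance, and isometric strength. Nothing in it names a derived circumference variable, a hypothesis or a favourable direction.

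The week-16 list is "TUG, 10 Meter Walking test, NMS, isometric strength both limbs", so circumference is not repeated there. A separate item, Other parameters, holds body weight and height.

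The Background reports that "the degree of strength loss was strongly associated with the degree of swelling (edema) in the operated limb (10"). It also defines sarcopenia as including loss of muscle mass and says that a hip fracture makes it worse. The Population section sizes the trial on a 30% reduction in the operated-versus-healthy strength difference: 38 per group, 80% power, significance level 0.05. The data analysis section says that "the primary analysis will be repeated measures analysis of variance (ANOVA) to determine the systematic difference between the intervention and control group" and names no covariate.

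**The concern.** A measurement taken at inclusion and again at discharge, listed under primary outcomes, reads as something to be compared between arms and reported as a main result. That requires knowing beforehand which direction is benefit. Circumference adds fluid and muscle together, and on the protocol's own account both matter after hip fracture, with opposite signs. A difference of either sign could then be presented as favourable after the fact, and a null result could hide two opposing effects. Which measurements count as primary is a matter the protocol itself fixes, so this cannot be left to a statistical analysis plan.

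**Working it through.** **1. Direction of benefit.** Take the operated limb from inclusion to discharge and compare strength-training patients with controls. The favourable directions come from the Background (swelling goes with strength loss; loss of muscle mass is a harm).

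| Difference in the training arm | Circumference | Reading |
|---|---|---|
| Less swelling | smaller | favourable |
| Less muscle | smaller | unfavourable |
| More muscle kept | larger | favourable |
| More swelling | larger | unfavourable |

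Each sign has one favourable and one unfavourable cause, and the protocol gives no rule for choosing.

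**2. Size of the ambiguity (illustration).** Treat the thigh as a cylinder with assumed circumference C = 45 cm; the protocol gives no limb size. Area A = C²/(4π), so a small change in area moves circumference by ΔC = 2πΔA/C. For an assumed ΔA of 5 cm², ΔC = 2 × 3.1416 × 5/45 = 0.70 cm, whether the tissue is fluid or muscle. If training keeps 5 cm² of muscle, the between-arm difference is +0.7 cm. If it clears 5 cm² of fluid, it is −0.7 cm. If it does both, it is 0.

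**3. Does measuring both limbs solve it?** Operated minus healthy is a reasonable marker of swelling at inclusion. By discharge, any wasting confined to the operated limb enters the same difference. Subtraction removes what the limbs share but does not separate fluid from muscle in the change.

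**4. What the trial is sized on.** The Population section gives no standard deviation, so 38 per group can be neither confirmed nor refuted. Solving backwards, two-sided (sidedness is not stated), normal approximation:

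- d = (1.960 + 0.842) × √(2/38) = 0.643 (0.651 with the t distribution).
- Implied SD = 0.30/0.643 = 0.467 of the mean between-limb deficit.

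These figures concern strength alone. Circumference has no effect size or sample-size basis.

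**5. Optional covariate.** Suppose the inclusion between-limb thigh difference has correlation r with re-test strength after baseline strength is accounted for. The protocol gives no coefficient, so r is assumed. The residual SD is multiplied by √(1 − r²), and

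power = Φ(0.643 × √(38/2)/√(1 − r²) − 1.960), where 0.643 × √19 = 2.802.

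| r | 2.802/√(1 − r²) | Power at 38 per group |
|---|---|---|
| 0 | 2.802 | 80% |
| 0.3 | 2.937 | 84% |
| 0.5 | 3.235 | 90% |

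If baseline strength already carries the information in the swelling, r is near 0 and nothing is gained.

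**The case against.** The best defence is that this block is an inventory of measurements, not a list of efficacy endpoints. It also contains the pre-operative New Mobility Score and the reasons for not performing a task, neither of which can be a treatment effect. No section makes an efficacy claim for circumference, week 16 drops it, and the reference to the earlier study hints at an edema reading. On this view the real defect is that no single primary outcome is singled out. Much of that is fair, and it limits the seriousness of the point. It does not cure the filing: the heading governs what counts as primary, and unlike the other misfiled items, circumference is a before-and-after measurement that could be analysed and reported as a primary result.

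Three stronger readings might be inferred and are not supported.

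- *That the plan errs by not adjusting for edema at inclusion.* Covariates are commonly left to a statistical analysis plan, which may exist but is not at hand. The association in the Background concerns patients being discharged to their own home, not values at inclusion, and comes without a coefficient. Prognostic value at inclusion is inference. Leaving a covariate out of a randomised comparison costs precision only; chance imbalance is already covered by the 0.05 error rate.
- *That the protocol states muscle size will fall in hospital and be preserved by training.* The Protocol Summary says "the elderly experience an average decrease in muscle strength of 15% after 10 days of bed rest", and the Lay Summary likewise anticipates less loss of strength. Both concern strength, not size. The support for mass is the sarcopenia statement in the Background, which gives no timing.
- *That circumference can show no effect at all.* A difference could be shown; what is undefined is its meaning.

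**Conclusion.** The point holds as a filing and definition defect: circumference stands under primary outcomes without a construct, derived variable or direction, and on the protocol's own background a between-arm change could not be interpreted as benefit or harm. It should be corrected, but it leaves the strength comparison and its stated 80% power intact. The conclusion rests on fluid and muscle both being able to change between inclusion and discharge, which the Background makes plausible but does not quantify; the 0.7 cm figure is illustrative.

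The covariate is a suggestion. Its value runs from about nil to 84% or 90% power, depending wholly on an assumed residual correlation.

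**What to change.** In Registrations, move circumference from Primary outcomes to Other parameters. Describe it there as a descriptive measure of swelling, defined as operated minus healthy limb at each time point, with no efficacy comparison. The cost is a wording change and the loss of a circumference efficacy result that could not have been interpreted. If the investigators do want it as an outcome, they would have to state the construct, the derived variable and the favourable direction in advance. This change does not settle which of the remaining measures is the single primary outcome.

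Optionally, name the inclusion between-limb thigh difference, measured before the allocation envelope is opened, as a prespecified covariate in the between-group strength analysis. It uses a measurement already planned and costs one degree of freedom.
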